### Recruitment & Randomization

Study staff review the schedules of participating chemotherapy infusion clinics weekly to identify potentially eligible patients. The list of potentially eligible patients is provided to staff oncologists for their approval prior to attempting recruitment.

Eligible patients are approached by research assistants after their second week of chemotherapy. Research staff explain the study to them, screen for eligibility, offer enrollment, and obtain informed consent. Patients agreeing to participate are asked to identify at least four potential caregivers using an algorithm based on the Norbeck Social Support Scale to determine the ranking of choices according to their involvement in the patient's life [32,33]. Research assistants then obtain contact information for the potential caregivers. Potential caregivers are recruited by research assistants by phone or in person if they accompany the patient to clinic. The research assistants explain the study, screen for eligibility, and obtain written informed consent. When a potential caregiver declines participation in the study, the research assistants contact the remaining potential caregivers on the list following the ranking provided by the patient. If no potential caregiver consents to participate, the patient is excluded from the study.

Patient participants are asked to identify preferred calling times for their ATSA calls. In addition, they are instructed on the use ATSA and rehearse an ATSA symptom assessment with the research assistant while in clinic. All patient participants are told to contact the project manager if they have any questions during their participation in the study and are given the telephone number for their respective oncology clinic for clinical issues not related to the study or when advised to do so by ATSA.

Basic sociodemographic and clinical data are kept on patients and caregivers who are ineligible for or refuse enrollment in order to understand the reach of the intervention in the broader population of eligible patients. In particular, we will describe the extent to which the requirement of caregiver Internet access serves as a barrier to recruitment among economically disadvantaged or rural patients.

After completing the baseline assessment, participating patients are randomized to either the control or intervention arm by a computer minimization program that balances the arms for type of cancer (lung vs. other) and the type of caregiver (in-home vs. out of home). The minimization procedure, known as 'adaptive randomization' balances trial arms according to the history of previous allocations. Arms are being balanced for lung cancer since patients with lung cancer have a symptom pattern distinct from patients with other solid tumors [34,35]. Arms are being balanced for type of caregiver because in-home caregivers have more access to the patient than do caregivers living at a distance and, hence, more opportunities for providing support.

### Comparison group

Patients randomized to the control arm of the study receive the Symptom Management Toolkit followed by weekly ATSA calls for 10 weeks. Caregivers in the control arm receive an email with a PDF copy of "What you need to know about cancer" from the National Cancer Institute (available from http://www.cancer.gov/cancertopics/wyntk/colon-and-rectal/page1). This booklet on cancer discusses possible causes, symptoms, diagnosis, treatment, emotional issues, and questions to ask the doctor.

### Intervention group

Patients randomized to the intervention arm receive the Symptom Management Toolkit and weekly ATSA calls for 10 weeks, as received by control-group participants. In addition, however, their caregiver receives weekly emails prompting them to log into the Cancer CarePartners website when their patient reports any core symptom severity of four or higher. The website informs caregivers of their patients' symptom assessment scores and provides them with advice for how to help, as described above. For the first 4 weeks in the study, staff monitor each caregiver's use of the website. When caregivers do not log into Cancer CarePartners within 48 hours of an assessment, staff telephone them to troubleshoot as needed.

### Data Sources

Data are being gathered from patient and caregiver surveys, ATSA, the Cancer CarePartners website, and medical record review.

#### Patient & caregiver surveys

Research assistants interview patients and caregivers by phone at baseline, 10 weeks post baseline, and 14 weeks post baseline. Patient surveys assess the study primary outcome (i.e. symptom severity) and secondary outcomes (i.e. physical and mental functioning, adherence to chemotherapy, and utilization of health services). Surveys also gather data on potential mediators of intervention effects (i.e. self-efficacy and actualized social support). Goals of the caregiver surveys are to measure caregiver outcomes (i.e. distress and burden). Patients and caregivers receive $15 for each completed survey.

#### ATSA

ATSA tracks call attempts, call outcomes (completed vs. incomplete), and reported symptom scores. The number of completed calls relative to call attempts will be used to describe patient uptake of the intervention as well as the dose received.

#### Cancer CarePartners website

The website tracks the number of email alerts sent to caregivers, numbers of log-in attempts, the web pages visited, the time spent per page, the tasks chosen, and caregivers' responses to the weekly task list survey. These data will be used to describe the usability of the website, as well as caregivers' choices of caregiving tasks from suggested options.

#### Chart review

A registered nurse reviews the patient's electronic medical record at week 14 or following withdrawal or death to assess covariates (e.g. comorbidities, supportive care received) and secondary outcomes (utilization, adherence with chemotherapy, and adverse events). The nurse reviews all inpatient and outpatient oncology notes written from four weeks prior to 14 weeks after informed consent. All modalities of cancer treatment and adjunct supportive care received during the observation period are noted (including consultations from palliative care services or referrals to hospice or home health nursing). Surgical procedures, the dose and duration of radiation treatment, and the dose and duration of chemotherapy (both recommended and actualized) will be noted, as will any medication changes (and reasons thereof).

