#### Adherence to chemotherapy

(source: medical record audit). Adherence to chemotherapy will be determined by the total number of dose reductions, infusion delays, and agent discontinuations.

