#### Utilization of services

(source: medical record audit). The utilization of inpatient and outpatient services will be measured in terms of the number of cancer-related: hospitalizations, visits to emergency or urgent care, scheduled and unscheduled contacts with oncology (in person or by phone), and referrals to home health or hospice.

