#### Primary Analytic Strategy

The primary effect of the intervention will be determined using data obtained at 10 weeks, and the sustained effect will be determined using data obtained at 14 weeks. Cross group comparisons will be made based on an intention-to-treat basis. We will also test the hypotheses with a longitudinal design by fitting a linear mixed-effects modelor a generalized linear mixed effects model to estimate effect averaged over 10 and 14 weeks, adjusting for potential within-person correlation and baseline values of the outcome variables [15].

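### The chart-review timing lets a withdrawn patient's record be read before week 14, which conflicts with the stated 14-week window and may undercount utilization, chemotherapy adherence events and adverse events

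*Protocol article*

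**What the plan says.** Under Chart review, the protocol article has a registered nurse go through each patient's electronic record "at week 14 or following withdrawal or death". The purpose includes "secondary outcomes (utilization, adherence with chemotherapy, and adverse events". The next sentence sets the period to be read: "The nurse reviews all inpatient and outpatient oncology notes written from four weeks prior to 14 weeks after informed consent". That window carries no exception for patients who withdraw.

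Two of these outcomes are defined as totals, with no mention of observed time. Under Adherence to chemotherapy: "Adherence to chemotherapy will be determined by the total number of dose reductions, infusion delays, and agent discontinuations". Under Utilization of services: "The utilization of inpatient and outpatient services will be measured in terms of the number of cancer-related" hospitalizations, emergency or urgent care visits, oncology contacts, and home health or hospice referrals.

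Under Primary Analytic Strategy: "Cross group comparisons will be made based on an intention-to-treat basis". Under Monitoring and Reporting of Adverse Events, patients who enter hospice may choose to come off study.

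**The concern.** Withdrawal is named beside death as an alternative trigger to week 14. If every chart were read at or after week 14, there would be no need to name it. The two events also differ: death closes the record, while a patient who stops calls or surveys can go on being treated at the same clinic. Eligibility even excludes patients who plan to move most of their care away from the study sites during follow-up. The later events would usually be in the record, and collecting them needs no contact with the patient.

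At stake are the chart-based secondary outcomes. Because they are counts, a chart that is read early yields a smaller number, and for these outcomes smaller mostly looks better. The Missing Data section need not catch this, since a shortened count can enter the dataset as an observed value. Leaving may also be related to the outcome: hospice entry is a route off study, and hospice referral is itself counted under utilization. For that reason an exposure offset, which assumes the same event rate after leaving as before, would not be a safe repair.

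**Working it through.** **The text.** Take a patient who withdraws at week 5.
- The timing sentence allows the review any time after week 5.
- The window sentence requires notes through week 14 after consent.
- A review at week 6 satisfies the first and cannot satisfy the second, because notes for weeks 7 to 14 do not yet exist. A review at week 14 or later satisfies both.

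Two nurses could each follow the timing sentence and count different periods.

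**Attrition input.** Sample Size Calculation gives 224 completing dyads, 25% attrition and a target of 300. Check: 224 / (1 − 0.25) = 298.7, so 299, which agrees with 300. Attrition is thus about 0.25 × 300 = 75 patients. It is not split by cause; if deaths are among them, those lose no chart events, so 25% is an upper-end figure for withdrawal.

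**Window lost if charts are read at withdrawal.** Let w be the share withdrawing and t the mean week of withdrawal. Neither is in the article, so both are assumed.

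Share lost = w × (14 − t) / 14

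| w | t | Calculation | Share of window lost |
|---|---|---|---|
| 5% | 10 | 0.05 × 4/14 | 1.4% |
| 5% | 3.5 | 0.05 × 10.5/14 | 3.75% |
| 25% | 10 | 0.25 × 4/14 | 7.1% |
| 25% | 7 | 0.25 × 7/14 | 12.5% |
| 25% | 3.5 | 0.25 × 10.5/14 | 18.8% |

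In the 12.5% row this is 75 × 7 = 525 of 300 × 14 = 4200 patient-weeks.

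**Effect on the arm comparison.** Assume no true effect, equal event rates in those who stay and those who leave, and mean withdrawal at week 7, so that each withdrawer loses half the window.

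Count ratio (intervention / control) = (1 − 0.5 w₁) / (1 − 0.5 w₀), where w₁ and w₀ are the withdrawal shares in the intervention and control arms

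- 25% in both arms: 0.875 / 0.875 = 1.00
- 20% control, 30% intervention: 0.85 / 0.90 = 0.94
- 15% control, 35% intervention: 0.825 / 0.925 = 0.89
- 30% control, 20% intervention: 0.90 / 0.85 = 1.06

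Equal withdrawal at equal times loses events but leaves the ratio unbiased. The unequal splits are illustrations; none is in the article.

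**The case against.** The strongest reply is that the article states no truncation. It says following withdrawal, not at withdrawal, sets no date for the review, and gives one window for everyone. A reader might infer that events after withdrawal are never counted; the text does not support that, because a later review of the full window is equally compatible with it. This stands. The defect is a conflict that arises if the review is prompt, and the article permits a prompt review.

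Second, the meaning of withdrawal is not given, and the full protocol and consent form are not shown. Where a patient revokes permission to use the record, ending the review is proper. This also stands and has to be an exception in any fix. It does not explain why a patient who only stops calls or surveys should be reviewed early.

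Third, the intention-to-treat sentence governs how patients are compared by arm and does not mention chart timing. Early review fits poorly with it but does not contradict it outright.

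Fourth, Attrition Analyses compares drop-outs and reasons for attrition by arm, so differential loss would be noticed. That is true, but seeing the imbalance does not recover the uncounted events.

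A reader might also infer that the error must favour Hypothesis 1a, more so if withdrawers are heavy users of care. Nothing in the article predicts that the intervention arm will lose more patients. Nor does heavier use by itself enlarge a false benefit. With twofold use among withdrawers and 20% against 30% withdrawal at mean week 7, counted events are 0.8 + 0.2 × 2 × 0.5 = 1.0 (control) and 0.7 + 0.3 × 2 × 0.5 = 1.0 (intervention), a ratio of 1.00. The full-window totals would be 0.8 + 0.2 × 2 = 1.2 and 0.7 + 0.3 × 2 = 1.3, a ratio of 1.08. The counts are distorted, by an amount that depends on who leaves and when.

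**Conclusion.** The point holds as an internal inconsistency. The timing sentence allows a withdrawn patient's chart to be read before week 14, the window sentence requires notes that would not yet exist, and the article does not say which prevails. Utilization, chemotherapy adherence and adverse events may therefore be undercounted in withdrawn patients.

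If charts are read at withdrawal, the loss is 1.4% to 18.8% of the post-consent window over the assumed range. The 12.5% figure (25% withdrawing at mean week 7) treats all attrition as withdrawal. Bias between arms needs a difference in withdrawal, its timing or withdrawers' event rates. The 0.94 ratio is one example, and the direction is not fixed in advance.

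Only chart-based secondary outcomes are affected; summed symptom severity comes from patient surveys. The change is worth making because it is cheap and because events nobody has read cannot be restored by modelling.

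**What to change.** Reword the timing sentence under Chart review so that the chart of every randomized patient is reviewed at or after week 14 for the full window. This should include patients who stop calls, stop surveys or come off study, for hospice or any other reason. Allow the window to close early only at death or where the patient withdraws permission to use the record, and record the observed time in those cases. State that utilization and chemotherapy adherence are analysed in all randomized patients on this basis.

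The cost is small: the same nurse reads the same record at a later date, with slightly more notes for withdrawn patients. Study procedures, and the consent wording if it does not already do so, must separate withdrawal from calls or surveys from withdrawal of record access.

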### Quality control

Research assistants rehearse an ATSA call with every patient participant at the time of enrollment. They review call data from ATSA regularly to identify patients who do not respond to scheduled calls. When patients do not respond to multiple ATSA attempts over 48 hours (at any period throughout the 10 weeks of the trial), research assistants contact them to determine the reason; reasons for non-compliance are tracked. Support is offered to patients whose reason for noncompliance relates to technical issues.

Similarly, for the first 4 weeks on the study, caregivers' Web logs are reviewed to identify caregivers who either have not been able to sign-in or create a task list. Research assistants contact caregivers whose Web logs indicate noncompliance and call caregivers to identify the cause. Depending on the reason for the difficulty, research assistants offer to guide the caregiver by telephone during their next online session. Research assistants track all reasons for noncompliance with the website.

Patients and caregivers are not permitted to use ATSA or the website until the baseline survey is completed. Data is entered into a clinical data tracking system that alerts staff of survey due dates and incomplete data. The date the baseline survey is completed determines the dates for the 10 and 14 week surveys. Up to 10 attempts are made to contact each subject or caregiver for scheduling an interview. Abbreviated versions of all interviews are available for patients who have difficulty completing the entire survey. Patients and caregivers receive a $15 gift card for each survey they complete. Monthly updates with comments on completeness of data are maintained and reviewed by the Project Manager.

The success of randomization is monitored quarterly by comparing the demographic and clinical characteristics of patients across study arms. Clinical staff is blinded to the assignment arm, as are the analysts examining the data.

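### The chart-review window is dated from informed consent rather than randomization, so events between the two can count as outcomes and post-randomization follow-up falls short of 14 weeks by an unstated lag

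*Protocol article*

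**What the plan says.** Chart review (under Data Sources) gives a single window: "The nurse reviews all inpatient and outpatient oncology notes written from four weeks prior to 14 weeks after informed consent". The stated purpose of the review is "to assess covariates (e.g. comorbidities, supportive care received) and secondary outcomes (utilization, adherence with chemotherapy, and adverse events", so the same window serves covariates and outcomes.

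The outcome definitions give no start date. Adherence is "the total number of dose reductions, infusion delays, and agent discontinuations", taken from the medical record. Utilization of services is likewise a set of counts from the record.

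Randomization comes after consent: "After completing the baseline assessment, participating patients are randomized to either the control or intervention arm by a computer minimization program". Before that, a caregiver must be recruited and must consent in writing. If one declines, "the research assistants contact the remaining potential caregivers on the list following the ranking provided by the patient".

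The surveys run on another clock: "The date the baseline survey is completed determines the dates for the 10 and 14 week surveys". The same section (Quality control) bars use of the telephone system and the website until the baseline survey is done.

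**The concern.** A randomized comparison of event counts should begin at randomization. Before that point the arms cannot differ because of treatment, so earlier events add the same expected number to both arms and pull the ratio of counts towards 1. Here the window opens and closes by the consent date, while patient consent is separated from randomization by caregiver recruitment and a baseline interview.

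Two things follow from the text. Events in the gap between consent and randomization lie inside the outcome window. And a window that closes 14 weeks after consent closes earlier than 14 weeks after randomization whenever there is a gap. The lost time depends on how long it took to find a willing caregiver, so it varies from patient to patient. The chart outcomes then also cover a different period from the 14-week survey outcomes in the same trial.

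Utilization and adherence are both named in Hypothesis 1a and in the study goal at the start of Methods, so a diluted comparison would weaken part of what the trial sets out to test.

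**Working it through.** The plan states no figure to reproduce here. The check is the order of dates, followed by window arithmetic under a stated assumption.

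**Order of events**
1. Patients are approached after their second week of chemotherapy and consent (Recruitment & Randomization). Eligibility allows entry up to 10 weeks after chemotherapy starts.
2. Patients name at least four potential caregivers in ranked order. Staff contact them by phone, or in person if they come to clinic, until one consents.
3. The baseline survey is completed. This date sets the survey clock.
4. The patient is randomized.

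The chart window is tied to step 1, read as the patient's consent because it is the patient's chart. The intervention can act only after step 4.

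**Inputs**
- Window: 4 weeks before to 14 weeks after consent, 18 weeks in all (Chart review).
- L = weeks from consent to randomization. This is not stated; 0 to 4 is an assumption.
- True rate ratio after randomization: 0.75, an assumption for illustration.
- Constant event rate over the window, also an assumption.

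**Post-randomization follow-up** = 14 − L weeks: 14 at L = 0, 12 at L = 2, 10 at L = 4.

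**Reading A: the look-back is baseline data only, and outcomes are counted from consent**
- Pre-randomization share of the counted time = L/14.
- Apparent rate ratio = [L + (14 − L) × 0.75]/14.
- L = 0: share 0%; ratio 10.5/14 = 0.75, no dilution.
- L = 2: share 2/14 = 14%; ratio (2 + 9)/14 = 0.79.
- L = 4: share 4/14 = 29%; ratio (4 + 7.5)/14 = 0.82.

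**Reading B: every event in the 18-week window is counted**
- Pre-randomization share = (4 + L)/18.
- Apparent rate ratio = [(4 + L) + (14 − L) × 0.75]/18.
- L = 0: share 4/18 = 22%; ratio (4 + 10.5)/18 = 0.81.
- L = 2: share 6/18 = 33%; ratio (6 + 9)/18 = 0.83.
- L = 4: share 8/18 = 44%; ratio (8 + 7.5)/18 = 0.86.

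**Limit of Reading B for adherence.** A patient who consents just after week 2 of chemotherapy has only about 2 of the 4 look-back weeks on treatment. Dose reductions, delays and discontinuations cannot occur before treatment starts. At L = 0 the ratio is then (2 + 10.5)/16 = 0.78 rather than 0.81.

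**The case against.** The strongest reply is that the section gives the range of notes the nurse reads, not the period over which outcomes are counted. One abstraction feeds covariates and outcomes together. Primary Analytic Strategy adjusts the longitudinal model for baseline values of the outcomes, and Hypothesis Testing applies an approach like the baseline-adjusted primary model to utilization and adherence. A baseline value for a chart outcome needs chart time before enrolment, and four weeks before consent would supply it. A condensed article may also leave exact counting rules to a fuller document.

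Much of this stands. A reader might infer that all look-back events enter the totals, and hence that 22% to 44% of the effect is lost. The article does not say that. The upper figure also needs an assumed four-week lag, and both need a constant event rate, which does not fit adherence events in early enrollees. Caregivers can be recruited in the clinic, so the lag may be short. If the consent meant is the caregiver's, the part of the lag due to caregiver recruitment disappears.

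The reply does not cover the interval from consent to randomization. Baseline use of the four earlier weeks leaves that interval on the outcome side of the window, and leaves the closing date tied to consent. The anchor is not an omitted detail: the article states it, and it disagrees with the anchor stated for the surveys.

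**Conclusion.** The point holds as a mismatch of anchor dates. Events between consent and randomization can count as outcomes, and chart follow-up after randomization is 14 weeks less a lag that is unstated and differs by patient. Whether the four-week look-back also enters the counts is left open.

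The size cannot be fixed from the article. If the look-back is baseline data only, there is no loss at zero lag and a true ratio of 0.75 appears as 0.82 at an assumed four-week lag. If every event in the window counts, the range is 0.81 to 0.86. Both sets assume a constant rate.

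A reader might go further and infer bias in favour of one arm. The documents do not support that: the look-back and the lag both precede allocation, so they are balanced between arms in expectation. The cost is dilution, noise and lost precision. Only chart-based secondary outcomes and adverse events are affected. The primary symptom score comes from surveys dated from baseline.

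**What to change.** Anchor the chart window to the date of randomization, which follows the baseline survey that already dates the other follow-up. Count utilization and adherence events only from randomization, to 10 weeks and to 14 weeks after it. The two cut-offs also settle a loose end: the study goal at the start of Methods places these outcomes at 10 weeks, while the chart window runs to 14. Say outright that the four weeks before randomization supply the baseline covariate and nothing else. Use the same start date for adverse events abstracted from the chart.

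The cost is a change to the abstraction form, a sentence of analysis text, and chart review that runs longer for each patient by the length of that patient's lag.
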